**Principal Investigator Name: [name]**

**A. SPECIFIC AIMS**

We seek to conduct a pilot RCT, examining the effects of a 10-week multimodal resistance exercise and creatine intervention (EXSUPP) (n=20) relative to resistance exercise and creatine placebo (EXPLA) (n=20) in sarcopenic individuals who have previously been treated for colorectal cancer. **Our overarching objectives are** to **1)** determine the feasibility and acceptability of the EXSUPP intervention with **creatine monohydrate supplementation** (0.10 g/kg/day) and **2)** understand the intervention characteristics that can be used to inform the design of a future large RCT. **Our RCT is *significant* because** it will establish the feasibility and acceptability of combining creatine monohydrate with resistance exercise training in the management of sarcopenia in individuals with colorectal cancer, providing preliminary support for the integration of effective lifestyle interventions in the management of colorectal cancer care. This pilot RCT will provide important information for the design of a future large-scale RCT R01 submission. To test our hypothesis and achieve the application objectives, we propose the following ***Specific Aims*:**

**Primary Aims: 1(a) To explore the feasibility and acceptability of a 10-week RCT comparing EXSUPP to EXPLA in individuals who are sarcopenic after colorectal cancer treatment.** This aim will be accomplished by assessing accrual, retention, adherence, and adverse events, **and 1(b) to quantify (mean change scores and precision estimates) and compare between-arm differences in muscular strength,** the primary variable used to diagnose sarcopenia.^2^ We hypothesize that we will be able to recruit (within a 12-month window) 40 colorectal cancer survivors, retain ≥75% of the sample, and achieve ≥75% adherence to the resistance exercise intervention and ≥75% adherence to creatine/creatine placebo supplementation, with no adverse events experienced throughout the intervention. For aim 1(b), we hypothesize that the EXSUPP arm will experience a more favorable muscle strength response than the EXPLA arm following the intervention. The trial will be considered a success if feasibility outcomes are achieved, and the hypothesized directionality of the EXSUPP intervention effects on muscular strength is observed.

**Aim 2. To obtain mean change scores and precision estimates and compare between-arm differences in secondary outcomes:** (a) body composition (whole-body and appendicular lean mass, whole-body fat mass and bone mineral content and density) (b) physical function, and (c) health-related quality of life measures.

**Exploratory Aim:** **Explore muscle molecular-level adaptations, i.e., mitochondrial health and protein turnover, in response to the interventions.** Cancer treatments have negative consequences on muscle cell signaling, mitochondrial health, and inflammation, and we will examine how these respond to exercise.

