**Primary Outcome:** The primary outcome of feasibility will be evaluated by **Response rates** (cases responding/cases ascertained (minus letters returned/not delivered & disconnected phone lines), and **reasons for ineligibility/disinterest** **and proportional accrual** (cases enrolled/cases ascertained) will all be tracked to inform feasibility of the trial. **Retention** will be calculated as the proportion of individuals who return for follow-up testing. **Adherence** will be calculated as proportion of total exercise achieved (outlined in “Intervention Fidelity”), and proportion of daily supplementation taken. **Adverse events** will be recorded, including a description of the event, its relation to the intervention, level of seriousness and intensity. To better understand program feasibility and acceptability, individuals will be asked to participate in qualitative in-depth exit interviews at the end of the study. A semi-structured interview guide will include questions that prompt participants to elaborate on their experiences and perceptions of the program and suggestions for how the program can be improved. Interviews will be audio-recorded, transcribed verbatim, and coded using inductive thematic analysis with Nvivo software(QSR International, Burlington, MA; USA).

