**Statistical Analyses:** For this feasibility study, we hypothesize that we will be able to recruit (within a 12-month window) 40 cancer survivors, retain ≥75% of the sample, and have ≥75% adherence to the intervention.^101^ In line with NIH guidelines on pilot studies, data obtained from these tests will be critical to optimize the intervention procedures and inform the design of a future RCT.^88^ **Further, the NIH reinforces that the “goal of pilot studies is to assess feasibility/acceptability of an approach to be used in a larger scale study”**^89^ Rather, our **sample size** is based on “practical considerations regarding participant flow, budgetary constraints, and the number of participants needed to reasonably evaluate feasibility goals.”^89,102^ To evaluate estimates of effectiveness for a larger RCT, we will test for differences in change in mean concentrations of muscle strength, body composition, physical function, quality of life, biomarkers (IL-6, TNFα, CRP) and mitochondrial health/muscle cell signaling among the groups using analyses of variance. We will calculate Cohen’s d by dividing the difference in group means (control versus supplement groups) by the pooled standard deviation. We will test for relations between 1) baseline levels of fatigue and inflammatory biomarkers and 2) changes in biomarkers and changes in fatigue using Pearson or Spearman’s correlations

**Timeline:** [name] has almost a decade of experience in executing exercise trials with cancer patients. We have an established infrastructure for recruiting individuals with cancer, testing our outcomes, and delivering interventions. Developing our database, training personnel, trial registration and submission of protocol paper for publication, will occur in the first 3 months of the grant. Participant recruitment will begin in month 4 of year one. Specifically, we will aim to conduct the intervention in 5 waves of 8-10 individuals in each wave. We anticipate identifying 4-5 eligible and interested individuals per month, allowing us to achieve our target or 8-10 individuals per wave across the study timeline.

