5. POTENTIAL RISKS

**Potential Risks.** There are no foreseeable major risks or side-effects associated with participation. However, as is the case with anyone who exercises, participation in the exercise intervention may result in mild discomfort and muscle soreness. There is also the possibility of muscle pulls or strains associated the exercise program, common to any type of physical activity. In order to minimize these risks participants will perform an adequate warm-up and cool-down before and after any exercise bout, be comprehensively instructed on the correct lifting technique, thoroughly familiarized with the movements involved in this investigation and supervised at all times by qualified professionals. If participants experience discomfort, soreness, or any issues with their prescribed exercise, the exercise prescription will be modified accordingly. Risk of falling may exist in the performance of some tasks, however, participants will be closely supervised to minimize the risk of a fall occurring. Furthermore, during exercise it is possible to experience symptoms such as shortness of breath, abnormal blood pressure, fainting, light-headedness, muscle cramps or strain, nausea, and in very rare cases heart rhythm disturbances or heart attack. These potential risks are common to any form of physical activity. During exercise training in other clinical populations, such as cardiac rehabilitation, rates of serious adverse events are very low at 1 in 49,565 patient training hours. Participants may also experience some anxiety in answering the items in the questionnaires.

Creatine is one of the most widely researched supplements, with over 1,000 studies confirming its safety in a variety of populations. As such, the risks of any possible side effects are minimal. However, participants receiving creatine might experience some mild gastrointestinal disturbance. The most commonly reported gastrointestinal disturbance is a mild stomach ache, or excess gas/bloating/loose stool. These side effects have been previously reported but occur in less than 5% of individuals supplementing with creatine. If individuals experience gastrointestinal distress, we will monitor the situation and they will be advised to stop supplementation if necessary. Due to the rarity and mild nature of symptoms, we don’t anticipate any lasting adverse reactions.

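### Read plainly, the trial's success rule demands zero adverse events of any grade or cause, although the protocol foresees and logs mild and unrelated ones

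*Protocol*

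**What the plan says.** Section A (Specific Aims) says of Aim 1(a): "This aim will be accomplished by assessing accrual, retention, adherence, and adverse events". One hypothesis sentence then sets a target for each measure: 40 recruited within 12 months, at least 75% retained, at least 75% adherence to exercise and to supplementation, and all of this "with no adverse events experienced throughout the intervention". The paragraph ends with the decision rule: "The trial will be considered a success if feasibility outcomes are achieved", together with a strength effect in the hypothesised direction.

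Three other places bear on this target:

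- **Section D, Primary Outcome.** Adverse events belong to the primary feasibility outcome. They "will be recorded, including a description of the event, its relation to the intervention, level of seriousness and intensity", but no threshold is given.
- **Section D, Statistical Analyses.** The feasibility hypothesis is restated as recruiting 40, then "retain ≥75% of the sample, and have ≥75% adherence to the intervention". Adverse events are not mentioned.
- **Section E.5, Potential Risks and Adverse Event.** The protocol states that "participation in the exercise intervention may result in mild discomfort and muscle soreness", and it mentions pulls or strains. Of gastrointestinal upset it says: "These side effects have been previously reported but occur in less than 5% of individuals supplementing with creatine". It also foresees bleeding, bruising and about a day of soreness after the optional biopsy. Event logs cover any adverse effect as well as disease-related and exercise-related events. The relatedness scale starts at not related and the intensity scale starts at mild.

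**The concern.** Section A gives adverse events no target other than zero, and the success sentence relies on the feasibility outcomes being achieved. Taken literally, one mild stomach ache, one strained muscle or one unrelated illness over 10 weeks would make the trial unsuccessful even if recruitment, retention and adherence all met their targets. Section E.5 foresees events of this kind and provides for grading them.

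The omission in Statistical Analyses adds a second problem, because the document then holds two lists of feasibility targets. If an event occurs, the choice between the lists could be made after the results are known. The success label is meant to support a larger trial, so its meaning should be fixed beforehand.

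**Working it through.** The protocol gives no probability of meeting the zero-event target, so there is no figure to reproduce. The check asks how likely the target is to be met.

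**Inputs from the protocol**

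- 20 participants per arm, 40 in total (Sections A and E.1).
- Gastrointestinal effects on creatine: below 5% (Section E.5). This is the only per-person event rate given.
- Earlier creatine trial: no adverse events in 30 recruited so far (Section C).
- Exercise programme: said not to have produced adverse events, with no denominator (Section D, Intervention).

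**Assumptions.** Participants are independent. The rate of any adverse event per person is not in the protocol, so a range is shown.

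**Formula.** If each of n participants has probability p of at least one event, P(no events) = (1 − p)^n.

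**Step 1: gastrointestinal events in the creatine arm only (n = 20)**

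- p = 5% (the ceiling): 0.95^20 = 35.8%
- p = 3%: 0.97^20 = 54.4%
- p = 1%: 0.99^20 = 81.8%

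This counts one type of event in one arm.

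**Step 2: any event in all participants (n = 40, rates assumed)**

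| Rate per person | P(no events in 40) |
|---|---|
| 1% | 66.9% |
| 2% | 44.6% |
| 5% | 12.9% |
| 10% | 1.5% |

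P(no events) falls below 5% once the rate exceeds 1 − 0.05^(1/40) = 7.2%, and below 1% once it exceeds 1 − 0.01^(1/40) = 10.9%.

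**Step 3: both sources together.** Take 5% for gastrointestinal events in the 20 creatine participants and an assumed rate q for any other event in all 40. Then P(no events) = 0.95^20 × (1 − q)^40:

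- q = 1%: 24.0%
- q = 2%: 16.0%
- q = 5%: 4.6%

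**Step 4: what the earlier experience shows.** For 0 events in 30 people, the exact one-sided 95% upper bound on the rate is 1 − 0.05^(1/30) = 9.5%. At that rate, P(no events in 40) = 0.05^(40/30) = 1.8%. The earlier result is therefore compatible with rates at which the target would nearly always be missed, and also with rates at which it would often be met.

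**Step 5: a serious-only target, for comparison.** Section E.5 quotes 1 serious event per 49,565 training hours in other clinical populations. Assuming one hour per session, 40 × 30 sessions give 1,200 hours. P(at least one) = 1 − (1 − 1/49,565)^1200 = 2.4%. This covers exercise only and borrows a rate from other populations. It indicates that a target restricted to serious events would nearly always be met.

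**The case against.** The strongest reply is that zero adverse events is a hypothesis and not a pass mark. The wording sits in a sentence of expectations, and the success sentence names feasibility outcomes without listing thresholds. The Primary Outcome paragraph only says that events are recorded and graded, and Statistical Analyses leaves them out. This shows that the sections disagree. It does not remove the problem, because Section A names adverse events as a measure of Aim 1(a) and offers no other threshold for them.

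The second reply is that the team has grounds for optimism: its earlier creatine trial and the exercise programme are both reported without adverse events. The team may also not count ordinary training soreness as an adverse event, since Section E.5 deals with soreness by modifying the exercise prescription. Both points are fair. However, 0 in 30 does not establish a low enough rate, and the protocol never says that soreness is excluded.

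A reader might go further than the documents allow in three ways:

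- **That the trial will almost certainly fail its own rule.** The only documented rate leaves at least a 36% chance of no gastrointestinal event on creatine. Near-certain failure needs an any-event rate of roughly 7% to 11% or more per person, which the protocol does not state.
- **That the protocol expects these events.** It words them as possible, uncommon or rare, and gives no expected count.
- **That Aim 1(a) cannot be answered.** Accrual, retention, adherence and adverse events are each tracked separately, and events are to be reported under CONSORT. Only the success label is affected.

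**Conclusion.** The success rule is wrong as written. On its plain reading it includes an unqualified zero-event target that conflicts with the events Section E.5 foresees and grades. That target has no counterpart in the Primary Outcome or Statistical Analyses paragraphs.

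The target is likely, though not certain, to be missed for reasons that say nothing about feasibility. The part resting on the protocol's own figure is the 36% chance of no gastrointestinal event among 20 creatine participants at the 5% ceiling. The wider range, from 67% down to 1.5% for no event of any kind in 40, rests on assumed rates of 1% to 10% and on independence between participants. The contradiction between the sections does not depend on which rate is true.

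**What to change.** In Section A, replace the unqualified zero-event target with one limited by the seriousness, relatedness and intensity scales already in Section E.5. One workable form is no serious adverse event related to the intervention; the sponsor should set the exact cut. State the same criterion in the Primary Outcome and Statistical Analyses paragraphs of Section D. Report all other adverse events descriptively by arm. If the sponsor does not intend adverse events to decide success, say so in all three places.

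The change costs a short amendment and collects no new data. It has two drawbacks. The target becomes less stringent. In addition, a serious-only cut would nearly always be met (Step 5) and would not register related, non-serious events of moderate or severe intensity, so those should be reported next to it.

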**B. BACKGROUND AND SIGNIFICANCE**

**
[figure not shown]
1.Significance: 1a. Sarcopenia is associated with reduced quality of life and reduced survival in colorectal cancer.** Colorectal cancer is the third most common cancer in the world.^3-5^ Sarcopenia, defined as the age-loss of skeletal muscle strength, lean mass and physical function,, affects up to 60% of individuals with colon cancer.^3-6^ Sarcopenia is associated with post-treatment complications and cancer-related and all-cause mortality.^7^ Individuals with colorectal cancer who are sarcopenic experience a 23% reduction in recurrence-free survival and a 9% reduction in cancer-specific survival.^8^ Left unaddressed, sarcopenia results in profound reductions in physical function and quality of life, and heightens mortality risk (Figure 1).

**Figure 1.** Accelerated musculoskeletal decline with treatment

**1b. Cancer treatments accelerate musculoskeletal decline and worsen outcomes.** Cancer treatments induce an accelerated aging phenotype that results in progressive loss in muscle strength, lean mass and physical function.^9-11^ Alterations in molecular signaling in **
[figure not shown]
**muscle as a result of cancer treatments exacerbate muscle dysfunction.^12,13^ In colorectal cancer, loss of lean mass during treatment is associated with a two- to four-fold increase in mortality risk.^14-16^ This is compounded by recent findings that at 6 months post-diagnosis, 54% of individuals diagnosed with colorectal cancer did not recover their pre-operative levels of physical activity..^17^ Consequently, colorectal cancer treatments exacerbate lean mass loss, accelerating the trajectory of a sarcopenic condition, poor functional status, and reduced quality of life(Figure 2).^14-16^

**Figure 2.** Contributions to and consequences of sarcopenia

[figure not shown]
**1c. Resistance exercise is a potent countermeasure to Sarcopenia.** Resistance exercise remains one of the most potent therapeutic strategies to target and potentially reverse the core components and consequences of sarcopenia (reduced muscle strength, lean mass and physical function) (Figure 3).^18-22^ Specifically, resistance exercise has been regularly demonstrated to have beneficial effects on muscle strength, lean mass and measures of physical function in a variety of cancer types.^21,23-28^ We have previously demonstrated that lifestyle interventions incorporating resistance exercise improve muscle strength, physical function (i.e. mobility) and lean mass in men with prostate cancer receiving androgen deprivation therapy.^29^ Importantly, in line with consensus statements from various international working groups, the goal of interventions in this space is not necessarily to *reverse sarcopenia*.^30,31^ Rather, successful interventions are those that improve clinically relevant outcomes such as muscle strength, physical functional status and health-related quality of life.^32,33^ Consequently, there is compelling evidence to suggest that resistance exercise training could target most, if not all components of sarcopenia, ultimately progressing an individual to a more robust status.

**Figure 3.** Resistance exercise as a countermeasure to sarcopenia

[figure not shown]

**1d. Creatine Supplementation augments adaptations to resistance training.** Resistance exercise alone is likely to be insufficient to completely overcome the multifactorial mechanisms influencing low muscle strength, lean mass and physical function in individuals with sarcopenia.^34^ Creatine is a naturally occurring compound synthesized in the body that plays a critical role in energy provision during resistance exercise. ^35-41^ Importantly, the rate of endogenous synthesis in the kidneys and liver (i.e. 1-3 g/day) and exogenous consumption of creatine through habitual dietary intake (primarily from red-meat and seafood), is roughly equivalent to the rate of excretion in the form of urinary creatinine (metabolic by-product of creatine).^36,42^ As such, the most potent and efficient way to increase intramuscular creatine stores is through supplementation. Creatine monohydrate is the most widely studied nutritional supplement to date, with well over 1,000 studies establishing its safety and effectiveness across the lifespan.^1,38,39,43-54^ Most relevant, creatine supplementation has been demonstrated to consistently yield superior improvements in lean mass when combined with resistance exercise training, relative to resistance training alone in older adults.^1,55^ Our group and others have also demonstrated superior improvements in muscle strength, lean mass and physical function with creatine supplementation and resistance training, relative to resistance training alone, particularly in older adults(Figure 3).^1,44,55^ Mechanistically, creatine supplementation may improve muscle protein kinetics, growth factors and satellite cells, calcium and glycogen flux, inflammation and oxidative stress, which could in turn improve sarcopenic status.^55-57^ The consistent and reliable improvements in muscle strength, lean mass and physical function indicate overwhelming potential for creatine supplementation to augment adaptations to resistance exercise and improve clinically relevant outcomes in individuals with colorectal cancer.

**Figure 3.** Creatine vs placebo effects on A) upper body strength, B) lower body strength and C) sit-to-stand^1^.

**1e. The need to understand molecular and cellular underpinnings that contribute to accelerated aging in cancer and how they impact the response to training.** An “accelerated aging” phenotype has been conceptualized to describe pathogenesis of anti-cancer therapies on key hallmarks of aging including DNA damage, inflammation and oxidative stress.^10,11,58^ Numerous mechanisms from preclinical models have been proposed as primary contributors to muscle dysregulation including skeletal muscle signaling, mitochondrial dysfunction, and heightened inflammation during treatment.^59-62^ For example, the ubiquitin proteasome system and autophagy-lysosome pathways have both been proposed as contributors to skeletal muscle atrophy with doxorubicin.^63-65^ Additionally, oxidative stress as a result of mitochondrial dysfunction has also been proposed as a contributor to doxorubicin and 5 fluorouracil induced atrophy.^66-70^ Interestingly, systemic inflammation (increases in Interleukin-6, TNF- α, Interleukin-1, etc.) has been associated with loss of muscle mass and function in other cancers and with other treatments.^12,71-75^ However, despite preclinical evidence supporting some of the proposed mechanisms, to date few clinical studies have investigated cellular alterations that contribute to changes in muscle biology because of treatment, and how this impacts exercise tolerance/adaptations. Investigating mechanisms of cancer-related musculoskeletal decline could help identify unforeseen barriers and targets for therapeutic interventions.

